
#### Secondary outcomes

Our secondary outcomes provide more insight into the mechanisms which might facilitate the use of SDM in ACP conversations. These include the view of participants on their competence, a measurement of the actual ACP policy at the ward level, and support from management. All secondary outcomes are measured by means of self-report questionnaires.The IFC-SDM measures nine behavioral aspects needed to engage in SDM and is based on the three-step talk model [16]. Each aspect is measured on three scales: how important participants find this behavior; how frequently they put this behavior into practice; and how competent they feel in doing so. To distinguish between the use of SDM in different work settings, the questionnaire assesses these behaviors in three circumstances: for conversations at the time of admission, during daily practice and in crisis situations. Items are scored on a 5-point Likert scale, ranging from ‘not important at all’ to ‘extremely important’. Participants can also indicate that they do not know. The IFC-SDM is based on earlier work by our research group and was pilot tested before the feasibility study [20]. No changes were made afterwards. The questionnaire is completed in the pretest stage, immediately after the last training session and after 3 and 6 months.The ‘Advance Care Planning Questionnaire’ (ACPQ) measures the organization of ACP at the ward level. 45 questions assess how and with whom ACP is discussed at the time of admission, in a crisis situation and at the start of palliative care. Answers are then compared with practice guidelines for communication on end-of-life issues for persons with dementia in nursing homes and scored either 0 or 1 for a total of 45 points. The higher the score, the more the guideline criteria are met. The ACPQ was piloted during the feasibility study in the form of a group audit [20]. This method was found to be too time-consuming considering the current sample size. It also did not allow for differentiating scores between care professionals and management staff. For this reason, the audit was turned into a questionnaire. One item was rewritten to reflect the underlying question better. The ACP is filled in by all participants at the pretest stage and after 3 and 6 months.The self-constructed ‘Supporting Advance Care Planning’ (SACP) assesses the support from management in discussing ACP and optimizing its organization (see Additional files 1 & 2). Participants answer eight items on two scales: how important they find the item and how much it is implemented at the ward level. These eight questions are based on the barriers which were most frequently mentioned at the end of the feasibility study. The items are scored on a 5-point Likert scale, ranging from ‘not important at all’ to ‘extremely important’. The questionnaire is filled in the pretest stage and after 3 and 6 months.

### Additional and control measures

Telephone interviews at 3 and 9 months after the last training session gauge participants’ progress in implementing the training components at the clinical, organizational and resident level (see Additional files 3 & 4). Barriers and facilitators are discussed, including recommendations for future research. A standardized form is created to ensure the interviews are conducted in a similar manner.Wards record a team meeting on ACP between training sessions. This requirement is part of a cross-sectional study which analyzes the correlation between the use of SDM in ACP conversations and the manner in which ACP is discussed during team meetings. The self-constructed instrument ‘Assessing Care Choices of the Elderly in Nursing home Teams’ (ACCENT) scores the audio files on 5 questions by means of a 5-point Likert scale, ranging from ‘*totally not agree’* to ‘*totally agree*’ (see Additional files 5 & 6). The questions are based on OPTION and pertain to the manner in which elicited care preferences are treated and followed-up, as well as the involvement of all team members in discussing the subject. The latter reflects our view that ACP should be a team-based effort.The following demographic variables of participants are measured: age, gender, educational status, profession and employee tenure. We also record if discussing ACP is part of their routine and if they received any previous training on SDM.

### Statistical analysis

Due to the cluster-randomized design of the study, longitudinal multilevel analysis (linear mixed modeling with random intercepts at both the clinical and the ward level) is used as the method of analysis. Since nursing homes can participate in the training with multiple wards, an additional organizational level is added as well. SPSS 25 is used for the analysis.

First, the effectiveness of ‘We DECide optimized’ on the primary outcome – the use of SDM in ACP conversations – is assessed. Second, the effectiveness of the training on the secondary outcomes – (1) self-perceived importance, competence and the use of SDM in ACP conversations, (2) ACP policy and (3) support from management – is examined. Separate analyses assess whether our demographic variables influence the primary outcome. Only significant predictors are added to the final model.

Differences in baseline characteristics between the intervention and control group are analyzed by descriptive analysis.

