### Required sample size

The required sample size is calculated through the clusterPower software package for R, which takes the cluster-randomized design of the study into account [27]. Using a power of 0.80, assuming unequal cluster sizes (x̄=5, σ_X_ = 1) and an intraclass correlation of 0, a sample of 32 nursing home wards per condition is needed at the 5% significance level.

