### Outcome measurements

#### Primary outcomes

Our primary outcome is the use of SDM in formal ACP conversations. This outcome is measured at both the participant and the resident level through 3 instruments, which are selected based on their usage in comparable (inter)national research and with regard to their psychometric properties. Both observational and self-descriptive instruments are used, since the triangulation of data is considered especially important to report on effective change management in an adequate manner. For measurements on the resident level, brief and easily accessible questionnaires are chosen so as not to overburden the person with dementia or his or her family. See also: Fig. 3. Study overview*.*OPTION-12 is a valid and reliable observational instrument which measures the involvement of patients by clinicians during consultations (α = 0.79) [28, 29]. Observers score 12 items on SDM on a five-point Likert scale ranging from ‘the behavior is not observed’ to ‘the behavior is exhibited to a very high standard’. In this study, we use the Dutch translation to assess the extent to which nursing home staff involve residents and their families during formal ACP discussions. Participating wards send in 2 audio files of formal ACP conversations at the pretest stage as well as 3 and 6 months after training. These audio files are recorded by the same participants at the different time points. Recordings are rated by two blind researchers. Both read through the OPTION training manual beforehand. During the course of the feasibility study, OPTION-5 was developed [30, 31]. Though the latter differentiates better between various levels of patient involvement, both show good interagreement and correlate well with each other [32]. For this reason and so as not to differentiate from the feasibility study, we continue to use OPTION-12 during the course of this study.The ‘Shared Decision Making Questionnaire’ (SDM-Q) is an internationally validated questionnaire which assesses the implementation of SDM in clinical conversations. It can be used to investigate the effectiveness of interventions which aim to increase said level of SDM [33]. It consists of 9 items which are rated on a six-point Likert scale ranging from ‘completely disagree’ to ‘completely agree’. It is filled in separately by both the healthcare professional (SDM-Q-DOC) and the patient (SDM-Q-9) to assess their view on the conversation. The instrument was translated and validated in Dutch (SDM-Q-DOC α = 0.87, SDM-Q-9 α = 0.88) [34]. For this study, the SDM-Q was used in conjunction with the OPTION audio files to compare data from both instruments. Residents and their families received a pre-stamped envelope which they can use to send the SDM-Q-9 to us without any involvement from the nursing home ward.The Dutch variant of collaboRATE is used to assess further the view of residents on their involvement in ACP conversations. [35] This questionnaire gauges the level of SDM in 3 items on a 10-point Likert-scale, ranging from ‘no effort was made’ to ‘every effort was made’. Both are discriminative as concurrent validity to other instruments, including the SDM-Q, is established [36]. For this study, collaboRATE is filled in at the same time as the SDM-Q and sent in the same pre-stamped envelope. Due to the limited amount of items, it should also be more accessible in situations where residents and families consider the SDM-Q to be too burdensome.

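### The final model's covariates are chosen by significance in the trial's own outcome data, and the plan does not say whether that model or the unadjusted one is the primary test

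*Protocol article*

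**What the plan says.** The Statistical analysis section sets out "linear mixed modeling with random intercepts at both the clinical and the ward level", plus a nursing home level. It names no fixed covariate. It takes the effectiveness on the primary outcome first and on the secondary outcomes second, and then adds: "Separate analyses assess whether our demographic variables influence the primary outcome". The next sentence is the rule at issue: "Only significant predictors are added to the final model".

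The candidates are in Additional and control measures. Five variables are called demographic: "age, gender, educational status, profession and employee tenure". A separate sentence follows: "We also record if discussing ACP is part of their routine and if they received any previous training on SDM". Whether these two items count as candidates is not stated.

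Under Primary outcomes, the use of shared decision-making is one outcome, but "This outcome is measured at both the participant and the resident level through 3 instruments". These are OPTION-12, SDM-Q and collaboRATE. SDM-Q has a professional and a patient form, so there are four scores.

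Settings/participants describes simple randomization of 48 homes, giving 34 and 31 wards. It names no stratification factor that would fix a covariate by design. Baseline differences between the groups are handled descriptively.

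**The concern.** Whether a variable influences the outcome can be judged only from outcome data. Under the stated rule, nobody can write down the final model until the outcomes are in. This is a rule that the article states, not a detail left to an unseen analysis plan, and it leaves several choices open:

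- which model carries the effectiveness claim;
- what counts as significant, since 5% appears only in the sample-size paragraph ("a sample of 32 nursing home wards per condition is needed at the 5% significance level");
- whether candidates are tested singly or together;
- whether selection is run for each score, or once on a score that is not named.

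At stake is whether the reported effect comes from one known model or from one of several defensible models chosen with results in view. In a trial of this size, a prognostic factor can also miss significance and be left out even when it is imbalanced between arms.

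**Working it through.** **The plan's own figure.** The rule comes with no figure. The only design figure, 32 wards per arm, does not bear on this point and cannot be reproduced, because no effect size is given. With 32 × 5 = 160 participants per arm, intraclass correlation 0, two-sided 5% and 80% power, it corresponds to (1.960 + 0.842) × √(2/160) = 0.313 SD.

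**Number of possible models.** Each candidate is in or out: 2^5 = 32 models per score with five candidates, 2^7 = 128 with seven.

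**Chance entry of irrelevant covariates.** Assume a 5% threshold and independent candidates with no true association. The probability that at least one enters is 1 − 0.95^(k × s) for k candidates and s scores.

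| | 5 candidates | 7 candidates |
|---|---|---|
| One score | 1 − 0.95^5 = 22.6% | 1 − 0.95^7 = 30.2% |
| Three instruments | 1 − 0.95^15 = 53.7% | 1 − 0.95^21 = 65.9% |
| Four scores | 1 − 0.95^20 = 64.2% | 1 − 0.95^28 = 76.2% |

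The last two rows also assume independence between scores. That is unrealistic, because the instruments rate the same conversations, so the first row is the one to rely on.

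**Do the selected sets agree across instruments?** This was simulated with 65 wards, seven candidates, screening one at a time at 5%, and an assumed correlation of 0.3–0.6 between three instruments. The sets were not identical in 57–63% of runs with no real covariate effects, and in 91–99% when each covariate explained 2–5% of variance.

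**Type I error.** In ward-level least-squares simulation (34 v 31 wards, seven candidates, 6,000 runs per setting), the treatment test rejected a true null in 4.8–5.1% of runs with selected covariates, against 5.0–5.2% with all seven fixed. There is no inflation.

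**Retention of real predictors.** With seven real predictors of 0.2 SD each, selection kept on average 2.1 of seven at 65 units and 3.5 of seven at 130 units.

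**Effect estimate and power.** With 65 units, predictors of 0.2 SD and a true effect of 0.5 SD, the mean estimate after selection was about 0.47, against about 0.50 with fixed adjustment: (0.50 − 0.47)/0.50 = 6%, with a range of about 5–7%. Power was 0.44–0.45 against 0.47.

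All simulations are simplified ward-level illustrations. The variances, correlations and covariate effects are assumed, because the article gives none.

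**The case against.** The strongest objection is that the section can be read another way. Effectiveness comes first, and the demographic analyses are called separate. That fits an unadjusted mixed model as the primary test, followed by a secondary look at predictors, which is close to the remedy proposed here. This stands: a reader might infer that the headline effect will come from the data-selected model, but the text does not say so. Nor does it say the opposite, and it does call the selected model final. The supportable point is the ambiguity.

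Other stronger readings also fail:

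- **Seven candidates, screened one at a time at 5%.** The wording supports five. Neither the threshold nor the form of screening is stated.
- **No correction of chance imbalance.** Covariates that are selected are adjusted for, and the rule favours those related to outcome. With seven predictors of 0.2 SD and 65 units, the SD of the treatment estimate was 0.279 unadjusted, 0.257 with selection and 0.259 with all seven, so selection recovers nearly all the precision. The attenuation offsets this: 0.47/0.257 = 1.83 against 0.50/0.259 = 1.93, in line with the lower power.
- **Effects not comparable between instruments.** In a linear model, different baseline covariates do not change the mean difference being targeted, and the instruments use different scales anyway.
- **Inflated type I error.** The simulations show none when the rule is applied mechanically.

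**Conclusion.** The concern holds in a limited form. The article commits to a final model whose covariates depend on the trial's outcome data and may differ between scores, and it does not identify the primary test. No covariate is fixed elsewhere by design or by statement.

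The numerical harm is small: no excess type I error, about 5–7% attenuation of a true effect, and 2–3 percentage points less power than fixed adjustment. The last two rest on assumed one-at-a-time screening at 5%, 65 independent units and predictors of 0.2 SD. The 22.6% chance of an irrelevant covariate entering rests on five independent candidates and a 5% threshold.

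The main harm is to credibility. The model is open, the analyst has discretion, and adjustment for prognostic factors after simple randomization of 48 homes is unreliable. The plan should be changed, but this is not a fatal flaw.

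**What to change.** Delete the significance rule. State that the primary test for each score is one mixed model with:

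- arm, time and arm-by-time;
- the pretest score, entered at ward or participant level where the same residents are not followed (the article says that the same participants record at each time point, but not that the residents are the same);
- a short covariate list chosen in advance from the variables already recorded, kept whatever its p-value and used for every score.

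With the pretest score as a covariate, time covers the follow-up measurements only. Report any predictor model selected by significance as exploratory, with no bearing on the treatment comparison.

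The cost is a few sentences, with no new data. The downside is a few degrees of freedom, and a small loss of precision if the chosen covariates prove not to be prognostic.

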## Discussion

This article deals with the design of a cluster-randomized controlled trial which measures the effectiveness of ‘We DECide optimized’, a communication training program for nursing home staff, on the use of SDM in formal ACP conversations. Due to the complex nature of dementia, it is crucial for residents and their families to be able to express their preferences and wishes in an informed and timely manner. Furthermore, both clinicians and residents hesitate to initiate conversations due to a lack of information and experience. ‘We DECide optimized’ addresses both concerns by training nursing home staff in the use of SDM: participants receive information on SDM and ACP and engage in various role-play exercises with help from an experienced trainer. One strength of this training is the inclusion of professionals from all backgrounds to engage the ward as a whole in discussing ACP. Furthermore, each ward delegates one member of management to stimulate the implementation of the training at the ward level. An additional strength of the training is our multi-level approach: by engaging the clinical, organizational and resident level, all stakeholders in ACP are invited to immerse themselves in conversation and further encourage person-centered care. The triangulation of data and the inclusion of both quantitative and qualitative data allows for extensive reports on the effectiveness of the training. It also allows us to report on facilitators and barriers for future interventions which seek to enhance the use of SDM in ACP conversations. One limitation is that enrollment in the training is voluntary: wards which are not motivated are not likely to participate. Since this is a single-blind trial (due to the control group receiving the training only at a later date) there should be no intentional bias on the part of the participants. Another limitation concerns the upper limit of 6 participants for each ward. Ideally, every staff member who engages in daily conversation with residents and their families should receive the training, thus truly achieving a ward-level approach to ACP. Since two wards receive training together, we set a maximum of 12 participants per group so as not to hinder interaction and assimilation. Participants are also stimulated to disseminate the training components and materials to other staff members and/or incorporate elements thereof into their own practice policy.

This study describes a hands-on, multi-level training approach to improve the level of SDM in ACP conversations. By providing tools to ward staff, engaging the management and informing residents and their families, ‘We DECide optimized’ aims to decrease evidence-based barriers and to provide all stakeholders incentives to engage in conversations about (care) preferences in an informative and participatory manner. The intervention also provides insight into policymakers and researchers concerning the long-term implementation barriers and facilitators for interventions which seek to enhance SDM.

## Abbreviations

ACP: Advance Care Planning
SDM: Shared Decision Making
